#### Heart rate turbulence quantification

2.2.4

HRT refers to the fluctuations of sinus heart beat cycle length caused by PVC beats (18). When a PVC beat occurs, it results in a shortened interval with the prior beats and this interval is termed coupling interval (couplI). A longer interval than that of a normal sinus beat is then followed, which is a compensatory interval (compI) (36). The HRT reflects the natural fluctuation of HR after the compI. If more than 10 beats are detected as PVC, we will conduct HRT analysis to compute turbulence onset (TO) and slope (TS) (19) for each PVC beat. TO is an indicator to reflect the vagal inhibition by quantifying the initial fast increase of heart rate (36) and calculated as Equation 6:

(6)
$$TO=\frac{\left(RR_{1}+RR_{2}\right)-\left(RR_{-2}+RR_{-1}\right)}{RR_{-2}+RR_{-1}}\times 100\%$$

where 
$RR_{1},RR_{2}$
 are two RR intervals immediately after compI, and 
$RR_{-1},RR_{-2}$
 are two RR intervals immediately preceding couplI.

TS is an indicator to reflect the vagal activation and is measured as the maximum positive regression slope over any 5 consecutive sinus rhythm RR intervals within the first 15 RR intervals after the compI (19). Therefore, the analysis for both HRT parameters will require at least 2 sinus rhythm RR intervals before couplI and at least 15 RR intervals after compI. For 1-h ECG segments, we will compute the mean of TO and TS across all detected PVCs to obtain an average value that represents the overall heart rate turbulence for the recording period.

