### Data analysis

2.2

Based on data from the currently recruited 550 patients, we found some incomplete ECG recordings of short duration, necessitating data analysis based solely on the ABP signal. To address this issue, we will conduct the eAD characterization on two fronts: one from both ECG and ABP waveforms, and the other from only ABP waveforms.

We will conduct non-invasive characterization of eAD by computing multiple indices over 24 h following admission, including heart rate turbulence (HRT) (18), time- and frequency-domain analyses of HRV and sequence analysis of BRS. First, we will slice the long-monitoring waveform into 1-h segments and assess the signal quality for both ECG and ABP segments. Next, the premature ventricular contractions (PVC) detection will analyze high-quality ECG segments. If more than 10 PVC beats for a given 1-h segment are detected, we will conduct HRT analysis on ECG waveforms (19). HRT is generally assessed by two parameters: turbulence onset (TO) and turbulence slope (TS). TO measures the initial acceleration and subsequent deceleration of heart rate after a PVC, while TS quantifies the rate of heart rate return to baseline. We will extract two time series from the ECG and ABP waveforms: one consisting of RR intervals from normal sinus beats, and the other comprising systolic blood pressures (sBP) from ABP pulses. We will then perform three analyses on these sequences: extracting root mean square of successive differences (RMSSD) and HRT from time-domain RR interval sequences, transforming RR intervals into the frequency domain to calculate the low- and high-frequency band ratio, and estimating BRS indices from RR intervals and sBP sequences. For eAD characterization based on ABP signals alone, we will compute autonomic indices from pulse interval sequences, excluding HRT due to the difficulty of detecting PVC beats without ECG waveforms. Figure 1 summarizes the entire procedure, with detailed explanations of each function block provided in the following sections.

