## Expected results

4

Quantification of individual eAD indices, defined as reduced RMSSD, reduced HRT, reduced BRS, decreased LF power, decreased LF/HF (45, 51) (less/greater than 2.5 SDs of age/sex-standardized values) measured over 24 h following admission.Quantification of eAD, defined as 3 or more (out of 5) indices less/greater than 2.5 SDs of age/sex-standardized values measured over 24 h following admission.

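### The heart rate turbulence threshold and hourly mean use all detected PVCs, while the plan's own interval requirement makes only some of them measurable

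*Protocol article*

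**What the plan says.** Two sections of the protocol article set the entry rule. Data analysis (2.2) states it per hour: "If more than 10 PVC beats for a given 1-h segment are detected, we will conduct HRT analysis on ECG waveforms". Heart rate turbulence quantification (2.2.4) repeats it: "If more than 10 beats are detected as PVC, we will conduct HRT analysis to compute turbulence onset (TO) and slope (TS"), to be done for each PVC.

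Section 2.2.4 then sets a condition on the neighbouring intervals: "the analysis for both HRT parameters will require at least 2 sinus rhythm RR intervals before couplI and at least 15 RR intervals after compI". Turbulence slope (TS) is "measured as the maximum positive regression slope over any 5 consecutive sinus rhythm RR intervals within the first 15 RR intervals after the compI". For the hourly value the section ends: "we will compute the mean of TO and TS across all detected PVCs to obtain an average value".

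The PVC detector (2.2.3) screens candidates on width and morphology. It has no rule on spacing or on surrounding sinus beats. HRT then feeds the definition of early autonomic dysfunction in Expected results (4): "Quantification of eAD, defined as 3 or more (out of 5) indices".

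**The concern.** Whether a PVC can be measured depends on its neighbours. PVCs in couplets, runs, bigeminy or trigeminy often lack the required sinus intervals. They still count towards the threshold of more than 10, and the averaging sentence takes them into the mean.

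Two things follow. First, the number that opens the analysis is not the number behind the HRT value, so the threshold does not secure a minimum of measurable PVCs. Second, if the averaging sentence is programmed as written, ectopic intervals fill the RR(-2) and RR(-1) places in Equation 6, and turbulence onset (TO) is biased. HRT is one of five indices in the eAD definition, and the Discussion lists its first use in severe TBI as the first novelty of the study.

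**Working it through.** The plan gives no figure to reproduce here. The check has three parts.

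**1. Detected against usable PVCs.** Beat sequences were constructed for one hour at an assumed 80 beats/min (80 × 60 = 4,800 beats). An interval is sinus if both bounding beats are sinus. The coupling interval ends at the PVC, and the interval after the PVC takes the compensatory place. *Strict* means 2 sinus intervals before and 15 sinus intervals after. *Literal* means 2 sinus intervals before and any 15 after, with at least one run of 5 consecutive sinus intervals among them for TS.

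| Pattern in the hour | Detected | Usable, strict | Usable, literal |
|---|---|---|---|
| Sustained bigeminy | 2,400 | 0 | 0 |
| Sustained trigeminy | 1,600 | 0 | 0 |
| One bigeminy episode | 11 | 0 | 1 for TO, 0 for TS |
| One run of 11 | 11 | 0 | 1 |
| Six couplets | 12 | 0 | 6 |
| Four triplets | 12 | 0 | 4 |
| Every tenth beat | 480 | 0 | 478 |
| 11 isolated PVCs | 11 | 11 | 11 |

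In sustained bigeminy and trigeminy the RR(-2) interval touches a PVC, so the 2-interval condition alone removes every PVC. For couplets the strict zero also depends on the compensatory place. If the pause after the couplet is accepted as the first PVC's compensatory interval, 6 of 12 qualify even under the strict rule. The range is therefore 0 to 6, and both ends fall short of the minimum.

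If PVC-level values are independent with equal variance, a mean over 6 PVCs has a standard error √(11/6) = 1.4 times that over 11. A mean over 1 PVC has √11 = 3.3 times.

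**2. Scattered PVCs.** With random placement, on average about 10.5 of 11 PVCs are usable under the strict rule, and 26 to 27 of 30. For exactly 11 PVCs, all qualify if the first has 3 beats before it, neighbours are at least 17 beats apart, and the last has 16 beats after it:

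- Placements that qualify: C(4800 - 3 - 16 - 10×16, 11) = C(4621, 11), out of C(4800, 11).
- Ratio ≈ (4616/4795)^11 = 0.66, so about 34% of such hours have 10 or fewer usable.
- At 100 beats/min: (5816/5995)^11 = 0.72, so about 28%.

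A simulation of only 200 hours at 80 beats/min gave 39.5%, with a standard error of √(0.395×0.605/200) = 3.5 points. That is compatible with the exact 34%.

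**3. Effect on TO if every detected PVC is averaged.** All intervals are assumptions: sinus 700 ms, 686 ms after the pause, coupling and inter-PVC intervals 450 ms, pause 950 ms.

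- Isolated PVC: (686 + 686 - 1400)/1400 = -2.0%.
- Second PVC of a couplet, where RR(-2) + RR(-1) = 700 + 450 = 1150: (1372 - 1150)/1150 = +19.3%.
- First PVC of a couplet, with the 950 ms pause as its compensatory interval: -2.0%.
- Ten isolated PVCs plus one couplet: (11 × (-2.0) + 19.3)/12 = -0.2%.
- If the first PVC of the couplet is dropped: (10 × (-2.0) + 19.3)/11 = -0.1%.
- Range for the 12-PVC mean: a coupling interval of 500 ms gives TO +14.3% for the second PVC and a mean of -0.6%. An interval of 400 ms gives +24.7% and a mean of +0.2%.

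**The case against.** The interval requirement stands directly before the averaging sentence. The natural reading is that the mean runs over PVCs that meet it, since otherwise the authors cancel their own rule one sentence later. On that reading the bias in part 3 does not arise. This is a fair reading and may be what is intended, but it repairs only the mean. The threshold, stated in two sections, still counts PVCs that cannot be measured.

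It can also be said that a condensed article leaves minimum counts to a fuller plan. That would answer silence. Here the article fixes the threshold, the requirement and the averaging unit, and they do not fit together.

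Three stronger readings might be inferred, and the documents do not support them:

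- *One couplet turns a clearly normal TO abnormal.* A mean of +1.3% results if the 450 ms inter-PVC interval is taken as the first PVC's compensatory interval: TO is then (950 + 686 - 1400)/1400 = +16.9%, and (10 × (-2.0) + 16.9 + 19.3)/12 = +1.3%. Section 2.2.4 describes that interval as longer than a normal sinus one, so 450 ms does not fit. Statistical analysis (3) calls a TO near 0% normal and gives no SD, so no crossing of the 2.5 SD limit can be shown.
- *An HRT result can rest on no PVCs.* With none usable, TO and TS cannot be computed. The hour simply has no value, and other hours in the 24 may supply one.
- *Couplets and runs always leave none.* The text does not call the 15 later intervals sinus, and the literal reading leaves a few.

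**Conclusion.** The conflict is real. The threshold and the hourly mean refer to detected PVCs, while the requirement in the same section limits which of them can be measured. In clustered ectopy the analysis can open on few or no usable PVCs: none in sustained bigeminy or trigeminy on any reading, and 0 to 6 of 12 for six couplets. For scattered PVCs the loss is small.

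If all detected PVCs are averaged literally, one couplet among ten isolated PVCs moves mean TO from -2.0% to about -0.2% under the assumed intervals. The effect on classification is unknown. So is the share of hours affected, because the documents do not say how often ectopy is clustered in this cohort. The wording of the 15 later intervals also matters by itself: with a PVC at every tenth beat, 0 or 478 of 480 qualify depending on it.

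**What to change.** In section 2.2.4, average TO and TS only over PVCs that meet the interval requirement, in place of all detected PVCs, and state that the 15 later intervals must be sinus. In sections 2.2 and 2.2.4, apply the existing minimum count to those same PVCs. Set HRT to not available for an hour below the minimum, and report the number of PVCs behind each HRT value.

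The change costs a sentence or two and a few lines of code. The price is lost HRT values in hours of mostly clustered ectopy, and also in some sound hours just above the threshold: about a third of hours with exactly 11 randomly placed PVCs (34% at 80 beats/min by the exact count, 39.5% in the small simulation).

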We will first classify 1-h ECG signals into PVC or non-PVC segments using an existing algorithm, which employs a Siamese network architecture to capture complementary information from two-lead ECG signals (29). During training, the model will take a pair of ECG signals as inputs. In each training iteration, the two signal modalities will take turns flowing through the encoder and the projector of this network. The learned features of one ECG channel will pass through the predictor to map to the latent space of features from the other ECG channel. We will optimize an agreement loss between the predicted latent feature vector of one ECG channel ECG and the projected latent feature vector of the other ECG channel. We will also optimize a supervised cross-entropy loss for the output of the classifier function, which takes the latent features of one ECG channel as inputs. Upon completion of training, only the encoder and classifier are preserved for subsequent predictions. During testing, the trained network can operate using single lead ECG independently, without necessitating an ECG signal pair. After the PVC segments are classified, we will adopt the algorithm in (30) to identify the PVC locations in two stages. In the first stage, based on the PVC morphological characteristics in high width, large amplitude and an abnormal waveform, we identify rough PVC beats through the quantification of these qualities with rules. In the second stage, we refine detection to reject false positive and normal beats. If a solitary PVC candidate is identified after initial screening and its morphology closely aligns with that of the majority of other beats, it should be reclassified as non-PVC and excluded from further consideration. Conversely, if there are multiple PVC candidates, their widths (cW) are computed at three-fourths the height of the smallest candidate. Subsequently, the PVCs are assessed pairwise. A PVC that exhibits considerable deviation from others and possesses a cW exceeding the mean is designated as an ectopic PVC. Candidates failing to meet these criteria are categorized as non-PVC and consequently excluded from the analysis.

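### Heart rate turbulence is triggered by, and averaged over, all detected PVCs, with no check of the short coupling interval and long pause by which the plan describes a PVC

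*Protocol article*

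**What the plan says.** All references are to the protocol article.

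- **Description of the event (section 2.2.4).** Of a PVC beat it says that "it results in a shortened interval with the prior beats and this interval is termed coupling interval". The next interval is described as longer than that of a normal sinus beat and named the compensatory interval. Turbulence is the heart-rate fluctuation that follows it.
- **How beats are located (section 2.2.3).** A learned classifier first labels ECG segments as PVC or non-PVC. Within PVC segments, "based on the PVC morphological characteristics in high width, large amplitude and an abnormal waveform, we identify rough PVC beats". A second stage then removes false positives by comparing candidates' morphology and width. No RR timing is mentioned in either locating stage.
- **Trigger (section 2.2, repeated in 2.2.4).** "If more than 10 PVC beats for a given 1-h segment are detected, we will conduct HRT analysis on ECG waveforms". The count is of detections.
- **Eligibility (section 2.2.4).** At least 2 sinus RR intervals before the coupling interval and at least 15 RR intervals after the compensatory interval. No limit is set on the length of the coupling or compensatory interval itself.
- **Averaging (section 2.2.4).** For each 1-h segment, "we will compute the mean of TO and TS across all detected PVCs to obtain an average value".
- **Use (sections 3 and 4).** Normal is given as TO near 0% and TS above 2.5 ms/RR. Reduced HRT is one of five indices, of which three or more must be abnormal for eAD.

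**The concern.** The plan describes the event by timing, but the steps it sets out never test timing. A sinus beat distorted by artefact, or a wide conducted beat, can look like a PVC in width and shape. In stable rhythm it meets the 2-before and 15-after rule automatically, because its neighbours are ordinary sinus beats. It then does two things: it counts toward the more-than-10 trigger, and it supplies a TO and a TS although there was no premature beat and no pause.

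At stake are the validity of the segment HRT values and the decision on which hours have an HRT value at all. HRT also feeds the eAD definition, so an error here reaches that classification.

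**Working it through.** The article states no error rate or expected count for this step, so there is no figure of its own to reproduce. Three checks were made.

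**1. Meeting the trigger on false detections alone.** From the article: more than 10 detections in 1 h. Assumed: 90 beats/min, so 60 × 90 = 5,400 beats/h; per-beat specificity s after all detection stages; independent errors; no true PVCs; no protection from the segment classifier. False detections X follow Binomial(5,400, 1 − s), and the trigger is met when X ≥ 11.

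| Specificity | Expected false detections/h | P(trigger met in an hour) |
|---|---|---|
| 99.5% | 27.0 | > 0.99 |
| 99.8% | 10.8 | 0.52 |
| 99.9% | 5.4 | 0.022 |
| 99.95% | 2.7 | 0.0001 |

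Heart rate matters too. At 99.8% the probability is 0.11 at 60/min, 0.37 at 80/min and 0.65 at 100/min.

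Hours with some true PVCs, but too few to qualify, are more exposed. At 99.9% and 80/min (4,800 beats/h, all true PVCs detected), an hour with 5 true PVCs needs at least 6 false ones: P = 0.35. An hour with 8 needs at least 3: P = 0.86.

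**2. Effect on TO.** Equation 6 compares the two intervals after the compensatory interval with the two before the coupling interval. Around a falsely flagged sinus beat, all four are ordinary sinus intervals. In a simulation (assumed mean RR 750 ms, RR SD 2 to 30 ms, lag-1 correlation 0 or 0.7, 40,000 runs each), mean TO for such beats was 0.00 to 0.08%. With false share f among averaged beats:

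mean TO = (1 − f) × true TO + f × (about 0)

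For an assumed true TO of −2%:
- f = 25%: 0.75 × (−2) = −1.5%
- f = 50%: 0.50 × (−2) = −1.0%
- f = 75%: 0.25 × (−2) = −0.5%

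**3. Effect on TS.** TS is the largest positive slope over any 5 consecutive intervals among the first 15, which gives 11 overlapping windows. A maximum over noisy slopes is positive even when nothing happened. Mean TS for falsely flagged sinus beats in the same simulation:

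| Assumed RR SD (ms) | Mean TS (ms/RR) |
|---|---|
| 2 | 0.9 to 1.0 |
| 5 | 2.3 to 2.5 |
| 10 | 4.5 to 5.0 |
| 20 | 9.0 to 9.9 |

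The plan's limit of 2.5 is passed once the RR SD exceeds about 5 to 6 ms. The false beats' TS thus reflects background variability and not a response to a PVC. The segment mean is (1 − f) × true TS + f × false TS, so it can move either way.

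**The case against.** **The article is a summary.** HRT computation and PVC location both follow cited methods, which may already filter on coupling and pause length. It could also be argued that a beat with no short coupling interval has no coupling interval in the plan's sense, so it drops out by definition. The first point cannot be settled from the article. But the article does state the trigger, the eligibility rule and the averaging rule, and averaging over all detected PVCs does not suggest a further filter. The concern is with the rules as stated, beyond any missing detail.

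**The detector is not final.** Section 2.2.3.1 will test several detectors and keep the best, and a learned network may use rhythm implicitly. This stands: a reader might infer that detection is purely morphological, but that describes only the beat-location step of the primary method. None of the alternatives is described with an explicit timing rule.

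**Safeguards exist.** There are signal-quality screening and lead selection, the segment classifier, second-stage rejection, and detector comparison on annotated databases using specificity and F1. These stand as well and will lower the false share, particularly in hours with no true PVCs. They do not remove it where true and false detections mix within a segment labelled PVC, and a clean but wide conducted beat is good-quality signal.

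**The size is assumed.** This is correct. Errors are also likely to cluster, which the binomial ignores. A reader might infer that patients without PVCs will routinely receive HRT values. The article supports no such statement: at 99.9% specificity or better the hourly chance is about 2% or less even with no segment screen.

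**The direction is unclear.** A reader might infer that preserved turbulence will look blunted and eAD will be over-called. The article does not support that. Section 3 treats TO near 0% as normal, whereas section 2.2.4 describes TO as the initial acceleration, which is negative by Equation 6. A pull toward zero reads as normal under one and blunted under the other, and a TS raised above 2.5 reads as normal.

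**Conclusion.** The concern holds in a limited form. As written, nothing after detection enforces the short-then-long timing by which section 2.2.4 describes a PVC. Falsely flagged sinus beats that survive the existing screens count toward the trigger and contaminate both means. TO shrinks toward 0% by the false share, and the TS contributed by these beats is a measure of background RR variability.

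The size is open, because it rests on a specificity that the article does not give. Under the stated assumptions the trigger problem is severe at 99.5%, substantial at 99.8%, small at 99.9% and negligible at 99.95%. Hours with some true PVCs remain exposed at 99.9%. The direction of any eAD misclassification is undetermined, and with three of five indices required, no change in classification has been shown. This is a cheap improvement worth making before HRT values are computed.

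**What to change.** In sections 2.2 and 2.2.4, replace the reference to all detected PVCs with confirmed PVCs. A confirmed PVC is a detection that meets both conditions:

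- its coupling interval is shorter, and the following interval longer, than the mean of the two preceding sinus intervals, by a margin fixed before any HRT value is computed;
- it satisfies the 2-before and 15-after rule.

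Apply both the more-than-10 count and the TO and TS means to confirmed PVCs only. The article gives no margin; it could be set on the annotated public databases already planned for the detector comparison.

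**Cost:** one eligibility sentence and a few lines of code. The intervals follow from the R peaks found in section 2.2.2, but the full beat series is needed, not only the sinus-beat RR series. Interpolated PVCs, which have no pause, are dropped, and some hours near the trigger lose their HRT value. The check would not exclude a premature, widely conducted supraventricular beat followed by a pause, so it adds to the morphological detection and does not replace it.

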#### BRS analysis

2.2.5

While heart rate changes due to acceleration and deceleration involve various physiological mechanisms beyond baroreceptor activity—including direct autonomic influences, mechanical factors, and other reflex pathways (37–39)**—**the combined analysis of baroreflex sensitivity (BRS) with directional heart rate changes offers a comprehensive view of autonomic regulation. This approach is particularly informative because the temporal relationship between blood pressure changes and subsequent heart rate responses helps distinguish baroreflex-mediated changes from other factors. Additionally, the magnitude and timing of these heart rate responses provide insights into baroreflex gain, even amid other regulatory influences. Analyzing both acceleration and deceleration also allows for the assessment of potential asymmetry in autonomic control, which is crucial in conditions like TBI where sympathetic and parasympathetic responses may be unevenly affected. By integrating these heart rate responses with traditional BRS measures, a more detailed understanding of cardiovascular regulation in sTBI patients is achieved, highlighting the complexities of impaired autonomic control.

We will use a phase-rectified signal averaging (PRSA) algorithm to compute BRS metrics. The process includes several steps regarding to the published paper (37):

Anchor points identification: if sBP values are higher than the preceding values, these values are defined as anchor points.For the synchronous RR intervals (RRI), each RRI is matched to a sBP value. A window length of 15-beat R-R intervals around each anchor point provides an optimal balance between capturing complete baroreflex responses and maintaining signal stationarity. Therefore, we select 15 RR intervals around each anchor point as a segment.Segments are aligned at the anchor points leading to a phase-rectification of the segments.Computation of PRSA signal: the PRSA signal 
$X\left(i\right)$
 is obtained by averaging the signals within the aligned segments, as shown in Equations 7, 8.

(7)
$$X\left(i\right)=\frac{1}{P}\overset{P}{\underset{p=1}{\sum }}RRI_{n_{p}}+l,\;l=-L,-L+1,\ldots ,L\text{.}$$

(8)
$$BRS=\frac{1}{4}\left[X\left(0\right)+X\left(1\right)-X\left(-1\right)-X\left(-2\right)\right]$$

where 
P
 is the total number of anchor points used in the averaging process. 
$RRI_{n_{p}}$
denotes the R-R interval values at the anchor point 
p
. 
$n_{p}$
 is the index of the anchor points with the total number of 
P
. 
l
 is an index representing a range around the anchor points from 
−L
 to 
L
, where 
L
 is the length of the segments before and after the anchor point considered for averaging. The expression 
$RRI_{n_{p}}+l$
 indicates the RR interval value at the position offset by 
l
 from the 
$p^{th}$
anchor point. 
$X\left(0\right),X\left(1\right),X\left(-1\right)$
and 
$X\left(-2\right)$
are the PRSA signal values at offsets 0, 1, −1, and − 2, respectively.

In addition, we will estimate BRS in the frequency domain (27). We will identify an autoregressive with exogenous input (ARX) model with sBP time series as input and RR interval time series as output, which is indicated as Equation 9 (40):

(9)
$$RR\left(k\right)=\overset{N}{\underset{i=1}{\sum }}a_{i}*RR\left(k-i\right)+\overset{N}{\underset{j=0}{\sum }}b_{j}*sBP\left(k-j\right)+e\left(k\right)$$

where 
$a_{i}$
 and 
$b_{i}$
 are coefficients of the ARX model and 
e
 is a random error with zero mean. We will then calculate the PSD of the transfer function within the LF frequency band (0.04–0.15 Hz) and the gain of the transfer function will be used as an estimate of BRS as Equation 10 (41):

(10)
$$\alpha \left(LF\right)=\sqrt{\frac{P_{RR}\left(LF\right)}{P_{BP}\left(LF\right)}}\text{.}$$

where 
$P_{RR}\left(LF\right)$
 and 
$P_{BP}\left(LF\right)$
 indicate the spectral densities in LF band of RR interval and sBP time series, respectively.

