## Statistical analysis

3

The characterization of eAD requires consideration of age-specific analysis. We will stratify patients into age to account for known age-related differences in autonomic function; Within each age stratum, we will establish reference distributions based on published normative data for that specific age group; For each autonomic measure, we will use age-appropriate reference ranges from healthy controls as reported in large-scale studies. Normally, RMSSD values should fall between 19 and 75 ms (48), HRT should exhibit a turbulence onset near 0% and a turbulence slope above 2.5 ms/R-R interval (49), and BRS is around 4.87–34.07 across different age groups over 20 years old (50).

For the determination of eAD, we will quantify the incidence and magnitude of anomalies such as reduced RMSSD, HRT, and BRS, alongside increased low frequency (LF) power and an elevated LF/HF ratio, which are critical indicators. eAD will be characterized if three or more of these indicators exceed or fall below 2.5 standard deviations from age and sex-standardized values. Autonomic function measures will also be considered as continuous variables as well. For the primary analysis, we will use data from patients over their first 24 h following ICU admission to identify eAD, as well as examine the association of these measures with clinical outcomes. In exploratory analysis, we will describe autonomic function measures over the first 5 days following ICU admission.

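### Equation 10 is not the ARX transfer-function gain the text says it is, Equation 8 is in ms, and one unitless range serves both BRS estimates

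*Protocol article*

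**What the plan says.** Section 2.2.5 (BRS analysis) of the protocol article defines two BRS estimates.

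- **PRSA (Equations 7 and 8).** "We will use a phase-rectified signal averaging (PRSA) algorithm to compute BRS metrics". Anchors are chosen from the pressure series: "if sBP values are higher than the preceding values, these values are defined as anchor points". RR intervals are averaged around the anchors, and BRS is a quarter of the contrast X(0) + X(1) − X(−1) − X(−2), where X is the averaged RR signal.
- **Frequency domain (Equations 9 and 10).** "We will identify an autoregressive with exogenous input (ARX) model with sBP time series as input and RR interval time series as output". The text then states that "the gain of the transfer function will be used as an estimate of BRS as Equation 10". Equation 10 is α(LF) = √(P_RR(LF) / P_BP(LF)), and its two terms "indicate the spectral densities in LF band of RR interval and sBP time series, respectively".

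Section 2.2 lists the indices as "time- and frequency-domain analyses of HRV and sequence analysis of BRS", a label that section 2.2.5 does not use.

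Section 3 gives one reference statement: "BRS is around 4.87–34.07 across different age groups over 20 years old". No unit, estimation method or choice of estimate goes with it. Reduced BRS is a single component of the eAD rule, which needs at least three of five indices more than 2.5 SD from age- and sex-standardized values (sections 3 and 4).

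**The concern.** There are two faults, both visible in the printed formulas.

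First, the sentence leading to Equation 10 and the equation itself describe different quantities. An analyst who follows the sentence uses the ARX coefficients. One who follows the equation never needs the model. The two answers differ most when RR variation is poorly explained by sBP, which is where a weak baroreflex would show itself.

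Second, Equation 8 is a time and Equation 10 is a time per unit of pressure, yet one range and one flag are provided for BRS. Unless the estimate behind the flag is named and matched to its range, the BRS component of eAD is not well defined, and at least one estimate would be judged on the wrong scale. The same metrics carry over to the ABP-only analysis (section 2.2.6), where pulse intervals replace RR intervals.

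**Working it through.** **Inputs from the article.** Equation 9 (coefficients a_i and b_j, zero-mean error e), Equations 8 and 10, the definition of P_RR and P_BP, and the range 4.87–34.07. RR is taken in ms, as the article does for RMSSD. Pressure in mmHg is assumed. The article states no BRS figure to reproduce.

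**Step 1: the gain of Equation 9.** With A(f) and B(f) the frequency responses of the a and b coefficients, the transfer function is H = B / (1 − A), and its gain is |B / (1 − A)|. Equation 10 contains no a_i, no b_j and no cross-spectrum, so it is a different quantity.

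**Step 2: how the two relate.** If e is uncorrelated with sBP,

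P_RR = |H|² · P_BP + P_noise, so √(P_RR / P_BP) = √(|H|² + P_noise / P_BP).

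The squared coherence is γ² = |H|² · P_BP / P_RR. With the gain roughly constant over the LF band, Equation 10 = |H| / √γ².

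| γ² | Equation 10 / gain = 1/√γ² |
|---|---|
| 0.9 | 1.05 |
| 0.7 | 1.20 |
| 0.5 | 1.41 |
| 0.3 | 1.83 |
| 0.1 | 3.16 |

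**Step 3: simulation check.** I simulated 200,000 beats from a model of the Equation 9 form. Assumptions not in the article: about 1 s per beat, sBP SD 4 mmHg with a peak near 0.1 Hz, AR coefficient 0.5, and RR noise SD 10, 20 or 30 ms. Gains are power-weighted over 0.04–0.15 Hz. With noise SD 20 ms (ms/mmHg):

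| True gain | Fitted ARX gain | Equation 10 |
|---|---|---|
| 11.15 | 11.16 | 11.67 |
| 5.95 | 5.93 | 6.85 |
| 2.97 | 2.94 | 4.51 |
| 1.49 | 1.49 | 3.74 |
| 0.74 | 0.73 | 3.50 |
| 0 | 0.04 | 3.42 |

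At true gain zero, Equation 10 returns 1.70, 3.42 and 5.13 for noise SD 10, 20 and 30 ms. The fitted model recovers the truth; Equation 10 levels off at a floor set by the noise.

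**Step 4: Equation 8.** It is a contrast of averaged RR intervals, so its unit is ms. Multiplying every sBP deviation by c leaves the anchors unchanged, because they depend only on whether sBP rose. It multiplies the sBP-driven part of RR by c. Equation 8 therefore tracks the product of gain and swing size. In the same simulation (noise SD 20 ms):

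| True gain | sBP SD (mmHg) | Equation 8 (ms) | Equation 8 / mean sBP rise at anchors |
|---|---|---|---|
| 5.95 | 4 | 6.57 | 3.29 |
| 2.97 | 8 | 6.54 | 1.64 |
| 11.89 | 2 | 6.55 | 6.57 |

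A fourfold range of gain (11.89 / 2.97 = 4.0) leaves Equation 8 unchanged. The divisor here is the mean one-beat rise, so the last column is proportional to the gain rather than equal to it. Its fourfold range (6.57 / 1.64 = 4.0) shows that normalisation restores the separation.

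**Step 5: the range.** Equation 8 is in ms and Equation 10 in ms/mmHg. A single range has one unit, so it can fit at most one of them.

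**The case against.** - **A reader might infer that neither formula yields what the reference range describes.** The article does not support that. Section 3 gives no unit or method, and 4.87–34.07 could rest on a spectral index like Equation 10. If it does, Equation 10 is the matching quantity and the gain wording is what is wrong.
- **A reader might infer that Equation 10 always overstates the gain.** That needs an open loop (e uncorrelated with sBP) and a constant or power-weighted gain. With feedback from RR to sBP, a cross term of either sign appears. Without noise, take a gain of 2 over half the band holding 80% of sBP power and 6 over the other half: Equation 10 gives √(0.8 × 4 + 0.2 × 36) = 3.22, below the unweighted mean gain of 4.
- **The sizes rest on assumed variances.** At high coherence the excess is about 5%. At zero gain the simulated value passes 4.87 (if that is in ms/mmHg) only with noise SD 30 ms. The rule works on 2.5 SD, and no SD is given, so no changed eAD flag is shown.
- **P_RR might mean only the sBP-driven model output.** Equation 10 would then equal the gain (5.95 against 5.95 in the simulation). The printed definition, however, refers to the RR interval series.
- **Pressure is not absent from PRSA.** It defines every anchor; only its amplitude is unused.
- **Sequence analysis may not be a third method.** It may simply mean analysis of the RR and sBP sequences that section 2.2 extracts.
- **Some of this is covered elsewhere.** Section 2.3 plans a coherence analysis, the introduction and discussion disclose vasopressor confounding, and section 3 promises age-appropriate ranges for each measure. An article may also leave detail to a fuller plan.

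These points limit the size and reach of the concern. They do not remove the printed contradiction at Equation 10, the difference in units, or the fact that the section 2.3 coherence is not stated as a condition on BRS.

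**Conclusion.** The point holds and should be fixed. Equation 10, as defined, is not the gain of the ARX model in Equation 9, and this needs no assumption. Equation 8 is in ms and is not a sensitivity per mmHg. With one range and one reduced-BRS indicator, at most one of the two estimates can be judged on its own scale.

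The direction of the Equation 10 discrepancy, towards masking reduced BRS, rests on an error uncorrelated with sBP and a roughly constant gain over the band. Its size runs from about 1.05 to 3.16 times the gain for squared coherence from 0.9 to 0.1. Which of these applies depends on RR noise and sBP variance that the article does not report. The effect on eAD incidence cannot be derived: BRS is one of five indices and three are needed.

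**What to change.** 1. **Make the section 2.2.5 text and Equation 10 agree.** Either compute the LF-band gain |B / (1 − A)| from the fitted ARX model, state how it is averaged over the band, and report it with LF coherence. Or call Equation 10 a spectral alpha index, drop the gain wording, and use it only where LF coherence reaches a stated minimum.
2. **Equation 8.** Divide it by the same four-point contrast of sBP at the same anchors, giving ms/mmHg, or do not compare it with a per-mmHg range.
3. **eAD rule.** Name one BRS estimate for the rule, with a reference range and SD from the same method and in the same unit. Keep the other as secondary. Apply the same choice to the ABP-only analysis.
4. **Section 2.2.** Reconcile the sequence-analysis label with section 2.2.5: describe it if it is a separate method, otherwise reword it.

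The cost is wording plus a minor recomputation from series and coefficients that the plan already produces. The choice of estimate should be fixed before eAD results are seen.
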